### Retention

Currently, trial participants have received their 6-month outcome assessment and will be due for their 12-month outcome assessment in January-February 2018. In order to maximize adherence and retention, we formed community advisory boards to monitor community satisfaction with implementation activities and to provide feedback to investigators in real time on any conflicts or dissatisfaction arising from project implementation activities. Lay health workers who facilitated the group sessions and the primary care health workers who supervised them were provided with a financial incentive as an appreciation of their commitment to the project. For participants who missed group sessions, the LHWs made home visits to re-engage them. Given that group sessions took place in the villages, the LHWs know the homes of the participants and have been able to mobilize them to return for their follow-up assessments.

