### Sample Size and Power Calculations

Primarily, our objective is to compare the proportion of subjects with mild to moderate depression in the intervention and control arms 6 months after the end of treatment. Based on results from our pilot project, we assume that the difference in proportion of depression cases at 6 months follow-up between intervention (15%) and control arms (25%) would be 10%. Using formulae proposed by Hayes and Moulton [48], and assuming the between-cluster coefficient of variation *k* of .25, a study with 12 nonmatched pairs of clusters, and a cluster size of 32 PLWH (total expected sample size of 768 PLWH) would have 80% power of detecting a 10% reduction in major depression cases at the 5% significance level. Table 2 illustrates the sample size and power calculations for various assumptions made. The number of clusters has been increased to 15 pairs to allow for individual level analyses using multilevel random effects regression models, and the cluster size was increased to 40, accounting for a potential 20% loss to follow-up.

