### Statistical Analyses

We will assess randomization across the two arms by comparing sociodemographic characteristics and other potential confounding variables using chi-square for categorical variables, and *t* tests or other equivalent nonparametric tests, as appropriate, for continuous variables. Primary outcomes will be the difference in follow-up proportions of participants who meet MINI criteria for major depression and difference in follow-up function scores of participants in the intervention and control arms 6 months after the end of treatment.

Secondary outcomes will include measures of self-esteem, posttraumatic stress symptoms, social support, stigma, alcohol use, ART adherence, viral load, number of disability days, asset possession indices, and cost-effectiveness data. Primary outcomes, secondary outcomes, and all subgroup analyses will be analyzed by ITT using a multilevel mixed model adjusting for clustering in health centers to determine effect modifiers [49]. The status of randomization (intervention/control) and baseline depression score will be included as a covariate. To account for the clustered design, we will treat clusters as a random effect. Potential confounding variables (eg, age, gender, socioeconomic status) with significant differences across intervention and control arms will be included as fixed factors. The R statistical software will be used to conduct all analyses [50]. A process evaluation using mixed methods to assess acceptability, feasibility, fidelity, causal mediating processes, and contextual influences in the trial will be conducted.

The primary analysis will follow ITT principles and use all available follow-up data, with missing data handled directly through maximum likelihood estimation in mixed modeling. We will document the extent and pattern of missing data and the reasons and will conduct sensitivity analyses of the impact of missing data on stability of the primary results. Missing values will be imputed with multiple imputations. We will verify that mixed model‒based results are not sensitive to violations of model assumptions with permutation tests.

Last, Cohen *d* effect sizes will be computed for the effect estimates to determine the size of the intervention effect [51].

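### The two missing-data methods named, likelihood and multiple imputation, normally share the missing-at-random assumption, so their agreement would say little about whether the primary result depends on who returned

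*Protocol article*

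**What the plan says.** The Statistical Analyses section says the primary analysis follows intention to treat on all available follow-up data, "with missing data handled directly through maximum likelihood estimation in mixed modeling". The team also "will conduct sensitivity analyses of the impact of missing data on stability of the primary results. Missing values will be imputed with multiple imputations". The role of the imputation (primary or sensitivity) and the imputation model are not given. Two related promises stand beside these: "We will document the extent and pattern of missing data and the reasons", and a check that mixed-model results are "not sensitive to violations of model assumptions with permutation tests".

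On loss and return, the Sample Size and Power Calculations section raises the cluster size to 40, "accounting for a potential 20% loss to follow-up". The Retention section says that "the LHWs know the homes of the participants and have been able to mobilize them to return for their follow-up assessments". Under Participant Eligibility Criteria, Recruitment, and Masking, the lay health worker (LHW) to whom participants are assigned is the person who delivers GSP or GHE to them.

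Table 1 lists MINI depression, function and the Self-Reporting Questionnaire at 0, 6, 12, 18 and 24 months, with none at month 2. The therapeutic-relationship scale and the attendance-based measures are listed at month 2.

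**The concern.** A sensitivity analysis for missing data is useful when it relaxes the assumption the primary analysis depends on. Likelihood in a mixed model and standard multiple imputation both assume that, given the observed data, non-return is unrelated to the unseen outcome. Fitted to the same information they estimate nearly the same quantity, so their agreement does not test that assumption.

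Two features of the design leave missing at random little to work with. Major depression on the MINI is an entry criterion, so baseline MINI status does not vary. On Table 1's schedule no outcome is measured between baseline and 6 months, so a participant missing at 6 months contributes almost nothing to the 6-month likelihood. There is also a reason to look: the LHWs who delivered the treatment also bring participants back, so return could be related to how treatment went.

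If GSP non-returners were depressed more often than GSP returners, with no matching excess in the control arm, the primary difference would be overstated. Both named analyses would still agree, and the result could be reported as stable.

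**Working it through.** **Inputs from the article.** 6-month rates 25% (control) and 15% (GSP); k = 0.25; 12 clusters per arm of 32 in the base calculation; 15 per arm in the trial; 20% potential loss; 1140 recruited, so 1140/30 = 38 per center.

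**Assumptions.** The planning rates apply among returners. The article gives no actual loss rates and no outcomes for non-returners, so those are varied below.

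**1. The plan's own figure.** With the unmatched-cluster formula for proportions, V = p0(1−p0)/n + p1(1−p1)/n + k²(p0² + p1²). At n = 32, V = 0.005859 + 0.003984 + 0.005313 = 0.015156. Then c = (1.960 + 0.842)² × 0.015156 / 0.10² = 11.90, rounded up to 12, with power 0.803, as in Table 2. Also 2 × 12 × 32 = 768 and 32/0.80 = 40. These figures are not in dispute.

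**2. Would the two methods diverge if return depended on outcome?** Take no true effect (25% in both arms) and 80% return in each arm.

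- If depressed GSP participants return at 60% (non-depressed at 86.7%), the observed GSP rate is 0.25 × 0.60/0.80 = 18.75%, a spurious difference of 6.3 points.
- If they return at 50%, it is 0.25 × 0.50/0.80 = 15.6%, a spurious difference of 9.4 points.

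A simulation (400 runs per scenario, 15 centers of 38 per arm) compared an available-data cluster-mean estimate, standing in for the mixed model, with within-center multiple imputation under missing at random. The estimates were 6.29 v 6.26 points and 9.19 v 9.14 points. They agree to within 0.1 point, and both are wrong.

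**3. How bad would non-returners have to be?** For loss m and rate q among GSP non-returners, the GSP rate is (1−m) × 0.15 + m × q. Control non-returners are held at 25%. SE = √(V/15) with n = 38(1−m), and a two-sided t test on 28 df. Worked case, m = 0.20 and q = 0.30: the GSP rate is 0.12 + 0.06 = 0.18; V = 0.1875/30.4 + 0.1476/30.4 + 0.0625 × (0.0625 + 0.0324) = 0.01695; SE = 0.0336; t = 0.070/0.0336 = 2.08; p = 0.047.

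| Loss | GSP non-returners depressed | Difference (points) | p |
|---|---|---|---|
| 20% | 15% (missing at random) | 10.0 | 0.004 |
| 20% | 30% | 7.0 | 0.047 |
| 20% | 35% | 6.0 | 0.09 |
| 20% | 40% | 5.0 | 0.16 |
| 10% | 50% | 6.5 | 0.056 |
| 5% | 60% | 7.75 | 0.020 |

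At 20% loss significance goes at about 31% on this basis. With a normal test and all 38 per center counted, it goes at about 34%. The difference reaches zero at (0.25 − 0.12)/0.20 = 65%.

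**4. The same odds shift in both arms, 20% loss.**

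- Odds ratio 2.43: GSP non-returners 30%, control non-returners 45%; overall 18.0% v 28.9%; difference 10.9 points, p = 0.0045.
- Odds ratio 4: 41% and 57%; overall 20.3% v 31.4%; difference 11.2 points, p = 0.006.

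The loss of significance in step 3 therefore comes from the asymmetry between arms.

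**The case against.** The strongest reply is that the text does not fix what is being criticised. The sensitivity analyses are promised without a method, and nothing confines them to multiple imputation or confines imputation to missing at random. A delta-adjusted analysis is itself multiple imputation, so it fits the wording. Such detail is often left to an analysis plan, which is not shown here, and the reasons for missingness will be documented. This stands to the following extent: a reader might infer that the promised check cannot reveal dependence on who returned, and the article does not support that. What remains is that the article does choose methods, and the pair it names does not test the assumption they normally share. The permutation tests address model assumptions, not non-return.

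A reader might also infer from the Retention section that return depends on the relationship with the LHW or on response to treatment, and does so differently by arm. The article does not say so. It presents LHW mobilisation as a retention aid, with no distinction between arms, and tracing people at home could equally reduce outcome-dependent loss. This part of the objection stands in full.

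Third, the unfavourable results need GSP non-returners alone to do worse, and the 20% is a planning allowance, not an observed loss. This also stands; steps 3 and 4 show how much depends on it.

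One caution runs the other way. The Data Collection and Management section describes primary and secondary outcome data as also collected after the group treatments (T1), which does not match Table 1. If a month-2 outcome exists, missing at random has more information to draw on, but two methods given the same data would still tend to agree.

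**Conclusion.** The point holds as a recommendation to strengthen the sensitivity analysis, not as evidence that the primary result is biased. The only missing-data methods named rest on missing at random as usually run. On Table 1's schedule they would agree almost by construction, so comparing them says little about dependence on who returned.

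The size depends on assumptions the article cannot settle. With 20% loss, 25% v 15% among returners, 15 centers of 38 per arm, k = 0.25 and control non-returners at 25%, significance is lost once roughly 31-34% of GSP non-returners are depressed. That is an odds ratio of about 2.5 to 2.9 against GSP returners. At 10% loss it takes about half of them. At 5% loss the result holds even at 60%. An equal odds shift in both arms leaves about 11 points. The article gives no figures from which to repeat this for the function score.

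**What to change.** Keep the missing-at-random analysis as primary. Define the promised sensitivity analysis as delta-adjusted (pattern-mixture) multiple imputation for both primary outcomes: shift the odds of MINI depression, and separately the function score, among non-returners. Vary the shifts independently in the two arms and report a two-way tipping-point table beside the loss rate in each arm. Include arm, center, baseline scores, sessions attended and the month-2 therapeutic-relationship score in the imputation model; the last two are already in the data collection schedule. Because the article reports the 6-month analysis as in progress, settle the range of shifts before results by arm are seen, or label the analysis as added later.

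The cost is analysis-plan wording and some programming, with no new participants or measures. The reported robustness may look less favourable, although at low loss the table would support the result. Changing contact procedures for the 12 to 24 month visits is not part of this fix, because it cannot affect the 6-month primary result.

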## Results

The trial has been approved by the Makerere College of Health Sciences School of Health Sciences Research Ethics Committee, TASO, and the Uganda National Council of Science and Technology. A Data and Safety Monitoring Board has been put in place to monitor trial progress. A total of 1140 persons living with HIV have been recruited to the trial. An analysis of baseline and 6-month data is in progress.

The results of this trial will not only be presented at national and international conferences but also submitted for publication in peer-reviewed journals and as a report to the funding agencies.

## Discussion

### Principle Findings

The GSP intervention is a complex intervention containing several interacting components, requires those delivering the intervention to acquire certain competencies and skills, and is associated with a variety of outcomes. Its development was prompted by the need to narrow the gap between the availability and need for depression treatment among HIV-positive populations in poor resource settings. The prior feasibility study [54] and pilot randomized clinical trial [36] of this intervention served to test these theories, procedures, recruitment, retention, and explore our hypothesized change processes and outcomes. The process evaluation data of this trial indicated that acquisition of knowledge and skills that enhance social connections, support, and better coping strategies with adverse situations leads to a reduction in depression symptoms. The absence of depression improves ability to work and obtain savings and other livelihood assets. The pursuit of livelihoods helps restore the dignity and independence that sustain a reduction in depression and improvement in functioning [37].

The Social, Emotional, and Economic empowerment through Knowledge of Group Support Psychotherapy (SEEK-GSP) trial will provide robust evidence for the change processes and outcomes we observed in the pilot studies. Further, the trial will demonstrate the potential for dissemination and integration into existing HIV service delivery platforms of a culturally sensitive first line treatment for mild to moderate depression. Depression poses a major burden on persons living with HIV/AIDS, particularly those in poor resource settings where poverty and mental health interact in a negative cycle [55]. Treating depression in PLWH is critical to the realization of the “90-90-90 targets” by 2020 aiming to diagnose 90% of all HIV positive people, provide ART for 90% of those diagnosed, and achieve viral suppression for 90% of those treated [56].

Prior trials of psychological therapies for depression in poor resource settings have shown that they result in significant reduction in depression symptoms and an increase in functioning levels [57,58]. However, both trials attracted mostly women. The SEEK-GSP trial specifically addresses this gap in evidence and in mental health services for a highly vulnerable HIV population in a primary care setting.

The SEEK-GSP trial targets both men and women living with HIV who have been exposed to decades of brutal civil war. Many of these individuals live in extreme poverty, with little to no education, in remote rural villages and rely on subsistence farming for survival. The vast majority have multiple experiences of war-related trauma and/or gender-based violence. This target group is a good example of what has been termed “intersecting populations”—groups that are vulnerable on multiple levels and disadvantaged across many determinants of health [59]. In this case, war survivors are made even more vulnerable by HIV/AIDS, unemployment, poverty, and food insecurity. Those living in remote villages with little access to services are even more vulnerable. This trial will demonstrate the extent to which primary care providers’ influence can be leveraged to motivate affected individuals to attend group sessions, manage issues that arise during engagement, and support practice of learned skills. Such primary care‒based interventions also provide health care system opportunities to support culturally appropriate services that minimize unintended negative impacts and maximize positive impacts for vulnerable groups.

### Limitations

Limitations of the SEEK-GSP trial relate to generalizability to other ethnic populations in Uganda. Also, the adherence measurement methods used in this study have limitations. However, to date there is no established gold standard to measure ART adherence. In the analyses of data from this trial, we shall assess the sensitivity of our adherence measure by determining whether it was able to predict viral suppression.

Despite these limitations, the trial will provide critical evidence to support culturally centered psychological therapy for depression in primary care settings. Trial outcomes will be supplemented with process evaluation outcomes that will provide contextual information that health care and public health stakeholders can use to guide implementation decisions for their particular setting [60].

### Conclusions

Confirmation of our primary hypothesis and supportive secondary data can critically inform the national dissemination and implementation of GSP to treat mild to moderate depression in PLWH. Results may provide greater insight into the partnerships between LHWs and existing government health systems in low-resource settings and may lead to policy formulation regarding the integration of GSP into HIV care services on a country-wide basis.

## Appendix

Multimedia Appendix 1 SPIRIT 2013 Checklist.

Multimedia Appendix 2 The content of group support psychotherapy and group HIV education group sessions.

Multimedia Appendix 3 Group support psychotherapy core competencies and subcompetencies.

Multimedia Appendix 4 Data safety and management plan.

## Abbreviations

AIDS: acquired immune deficiency syndrome
ART: antiretroviral therapy
GHE: group HIV education
GSP: group support psychotherapy
ITT: intention-to-treat
LHW: lay health worker
MINI: Mini International Neuropsychiatric Interview
PHC: primary care health center
PLWH: person living with HIV
SEEK-GSP: Social, Emotional, and Economic empowerment through Knowledge of Group Support Psychotherapy
TASO: The AIDS Support Organization
WHO: World Health Organization
